## Methods

### Design

This is a 12-week randomised controlled trial consisting of three groups randomised to exercise or usual care (Fig. 1). Participants will be randomised to one of three groups: a blood flow restriction cycling exercise training group (BFR-C), a non-blood flow restriction cycling exercise training group (CYC), or a non-exercising, usual care control group (CON).

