### Recruitment and screening of participants

Participants will be recruited through recommendation and referral from treating physicians at a number of dialysis clinics linked to a major public hospital service in a large metropolitan Australian city. Additionally, nurse unit manager recommendations and fliers briefly outlining the study posted within the dialysis clinics will be used to help identify prospective participants. Prospective participants will be screened initially face-to-face or via telephone by a member of the research team. Following this, confirmation from the treating physician will be obtained if not implied by referral. Participants will be required to provide written, informed consent prior to participation in the study.

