### Inclusion and exclusion criteria

Eligible participants will be male and female stable chronic (>3 months) haemodialysis patients aged between 18 and 80 years. Participants will be deemed medically eligible by their treating physician before participation in the present study. Participants will be excluded if they do not understand English and are unable to complete or comprehend the surveys or study documents; if within the previous 12 weeks they have participated in regular physical activity or sport (>150 min.wk.^−1^) of moderate or greater intensity [44], or structured resistance training (> 1 session.wk.^−1^); if they have symptomatic peripheral vascular disease, limb ischemia, untreated symptomatic cardiovascular disease, or any other absolute contraindications to exercise training (such as musculoskeletal factors or neurological conditions) that may affect their ability to perform physical assessments or exercise training protocols in the present study; if they are currently smokers; or if they are pregnant or have required hospitalisation for non-dialysis reasons in the 4 weeks prior to the study’s commencement. Patients will also be deemed unable to exercise during individual dialysis sessions if they present with fluid overload (> 5% above dialysis base weight) as this can cause reduced cardiovascular reserve [45]. Similarly, if patients have systolic blood pressure > 180 mmHg, or diastolic blood pressure < 90 mmHg prior to exercise they will be deemed unsuitable for exercise on that day (excluding the first blood pressure reading before dialysis, which is known to be unreliable) [46]. Of clinical concern is the known propensity for HD patients to become hypotensive (potentially more so post-exercise) during dialysis [47]. Although this is uncommon and our pilot data indicates this is not exacerbated by blood flow restriction, to ensure the safety of all patients they will be monitored for chest pain/discomfort, dyspnoea, lower limb pain, symptoms of severe hyper- or hypotension, and other signs of adverse events, which will be reported to the ethics committee of both the treating hospital and Deakin University.

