### Randomisation

Randomisation will be conducted at a participant level prior to familiarisation and baseline testing, and will randomise participants by blocks of 4 via a computer-generated random number sequence by an independent researcher. Blinding of intervention group to clinical staff and participants will not be possible once the intervention commences.

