### Exercise intervention

Exercise training sessions will occur intradialytically for all exercising participants and will be completed within the first 2 h of the session to avoid loss of exercise training quality [24, 48]. All sessions will be supervised by a member of the research team. Exercise training sessions will consist of cycle exercise for both BFR-C and CYC groups. Both BFR-C and CYC groups will complete a total volume of 20 min cycling at a relative intensity for each participant to be dictated by rating of perceived exertion (RPE), similar to previous exercise and ESKD studies [17, 49, 50]. This will also be compared to measurements of percentage age-predicted maximum heart rate (APHR_max_) in order to determine if targeted RPE needs to be adjusted to account for potential discrepancies between patient subjective intensity and objectively observed intensity. If participants are unable to maintain the prescribed cadence at this workload for the full duration, they will be instructed to complete as much of each cycling bout as possible.

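### One small, published block size in an open three-arm trial lets anyone tracking all past assignments know some upcoming ones for certain

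*Protocol article*

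**What the plan says.** The Design section of the protocol article sets up three arms: "Participants will be randomised to one of three groups". The Randomisation section gives one block size and the person responsible: the procedure "will randomise participants by blocks of 4 via a computer-generated random number sequence by an independent researcher". It places the step early ("Randomisation will be conducted at a participant level prior to familiarisation and baseline testing") and accepts that the trial is open: "Blinding of intervention group to clinical staff and participants will not be possible once the intervention commences".

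Other sections show who has a say in entry and who sees assignments:

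- Recruitment and screening: "Participants will be recruited through recommendation and referral from treating physicians at a number of dialysis clinics". Nurse unit managers also recommend patients. Then "Prospective participants will be screened initially face-to-face or via telephone by a member of the research team".
- Inclusion and exclusion criteria: "Participants will be deemed medically eligible by their treating physician before participation in the present study".
- Exercise intervention: "All sessions will be supervised by a member of the research team".
- Blood flow restriction procedure: limb occlusion pressure is measured at a familiarisation session, and only in those allocated to BFR-C.

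The article does not say how four places are divided among three arms, or whether there is one list or one per clinic.

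**The concern.** In a permuted block of known size, the last places follow from the earlier ones. When the earlier assignments can be seen, part of the sequence stops being random to whoever has been counting. An independent researcher protects the list itself, but does not prevent this deduction.

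Here the size is small, constant and published, and the arms differ visibly. The research team has a part in both screening and supervising. Someone who knew the next arm could time an approach to a patient, or lean on a borderline eligibility judgement, so that fitter or more willing patients went to one arm. The four primary outcomes (leg extension strength, six-minute walk, sit to stand, timed up and go) all depend on fitness and effort. The analysis described is a one-way ANOVA between groups, which would not remove such a difference.

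This is separate from the fact that 4 is not a multiple of 3. Correcting the size to a fixed 3 or 6 would cure the indivisibility and leave the predictability.

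**Working it through.** **Inputs.** Three arms (Design); block size 4 (Randomisation); 75 participants (Sample size calculation: 20 per group, 20% attrition, 20 / 0.8 = 25 per group, 3 × 25 = 75). The article gives no figure for predictability, so there is none to reproduce.

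**Observer.** Someone who knows the block scheme and every past assignment in order. This is the worst case. Two quantities are computed: the share of assignments known for certain, and how often the best guess is right. Chance is 33.3%.

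**Reading A: each block holds one of each arm plus one extra, the extra arm chosen at random.** The fourth place is certain when the first three already show a repeat. The first three are all different exactly when the fourth is one of the two places of the doubled arm, which has probability 2/4. So the fourth place is certain half the time and no earlier place ever is: (0 + 0 + 0 + 1/2) / 4 = 12.5%. The best guess by position is right 1/3, 5/12, 7/12 and 2/3 of the time, a mean of 2/4 = 50.0%.

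**Reading B: the same arm is always doubled (2:1:1).** The fourth place is always certain. The third is certain when the first two are the two single arms, with probability (2/4)(1/3) = 1/6. Share: (1/6 + 1) / 4 = 29.2%. Best guess: (0.5 + 0.5 + 0.583 + 1) / 4 = 64.6%.

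**Reading C: 4 means four per arm, a block of 12.** For a fixed block with m places per arm, the certain places are the final run of one arm. Its expected length is 3m/(2m + 1) out of 3m places, so the share is 1/(2m + 1). With m = 4 this is 1/9 = 11.1%. Best guess 51.2%, by exact recursion.

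**Alternatives.** The same formula gives fixed blocks of 3 and 6. Random sizes were simulated (1,500 runs of 75 assignments), with an observer who knows the set of sizes but not their order.

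| Scheme | Certain | About how many of 75 | Best guess right |
|---|---|---|---|
| 4, random extra arm | 12.5% | 9 | 50.0% |
| 4, one arm always doubled | 29.2% | 22 | 64.6% |
| 4 per arm (12) | 11.1% | 8 | 51.2% |
| Fixed 3 | 33.3% | 25 | 61.1% |
| Fixed 6 | 20.0% | 15 | 56.1% |
| Random 6, 9, 12 | 2.4% | 2 | 52.3% |

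**From exposure to bias.** The most that certain places alone could move an arm's mean is the share of that arm's places that are certain, times an assumed advantage of the steered patients. By arm the shares are 11.1% (C), 12.5% (A), and under B 33.3% for the doubled arm ((1/2 + 1/6) of its 2 places) or 25% for a single arm (1/4 of its 1 place). For an assumed advantage of 1 to 10 percentage points of strength change, the ceiling runs from 0.1 (0.111 × 1) to 3.3 (0.333 × 10) points. The documents give no value for the advantage.

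**The case against.** Four objections carry weight.

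1. **Who can see what.** The percentages need an observer who knows every past assignment. Recruitment spans several clinics. If one list runs across them, a physician or nurse sees only local patients and can deduce much less; if each clinic has its own list, the full figures apply locally. The article does not say which. It is also an inference that the team member who screens has tracked all assignments. This stands, and makes the figures upper bounds.

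2. **Delay.** Randomisation precedes familiarisation and baseline testing, and control participants have no sessions, so clinic staff may not tell them from patients yet to start. This stands for clinic staff. It is weaker for the research team, because the occlusion pressure measurement marks BFR-C participants at familiarisation.

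3. **The remedy does not improve guessing under every reading.** With a random extra arm the best guess is right 50.0% of the time now and about 52% after the change. It falls clearly only if one arm is always doubled (65% to 52%), which the article does not state. Someone steering patients could act on a good guess. This stands: the benefit is in certainty only.

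4. **Concealment.** A reader might infer that allocation is not concealed. The article is silent on who holds the list and when assignments are released, but a condensed article may leave that to the full protocol, and it does name an independent researcher. No fault is found there.

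**Conclusion.** The point holds as one of exposure. Under every reading of the block size tested, an observer with the full assignment history would know some upcoming assignments for certain: about 11%, 12.5% or 29%, or roughly 8 to 22 of 75. These are upper bounds, strongest for the research team, which both screens and supervises. They rest on the assumption that all past assignments are known in order.

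Two stronger readings are not supported. One is that referring physicians and nurse managers could in general foresee assignments; that depends on the list structure, which is not stated. The other is that the bias has a known size. A reader might multiply the overall certain share by a 10-point advantage and call the result the shift in the BFR-C mean. But 10 points is the whole planned difference between BFR-C and CYC (12 − 2), nothing in the article supports it as a selection effect, and the certain share differs by arm if one arm is doubled. Only the range of ceilings above can be shown, and it depends on the assumed advantage.

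The change is worth making because the block size has to be corrected for three arms anyway, and a fixed 3 or 6 would still leave 33% or 20% of assignments certain.

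**What to change.** When the block size in the Randomisation section is corrected for three arms, replace the fixed 4 with permuted blocks of randomly varying size in multiples of three, for example 6, 9 and 12. Do not substitute a fixed 3 or 6. Withhold the sizes from recruiting and supervising staff, and from publications, until recruitment ends. For assignments not yet made, certain ones fall to about 2.4%, even if the set of sizes becomes known. Guesses will still beat chance.

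The cost is a regenerated list and one amended sentence, with no extra staff or patients. If recruitment stops mid-block the arms may differ by a few participants; a block of 12 holds four places per arm, so the gap between two arms cannot exceed four.

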### Sample size calculation

The most relevant outcome for blood flow restriction training studies is knee extensor muscle strength, and this was used as the main primary outcome measure for calculating required sample size. Based on data from previous blood flow restriction research [25, 29, 32, 33], and previous exercise for ESKD research [18, 42, 43], the projected percentage changes in knee extensor muscle strength for each of the three groups are CON = −3%, CYC = 2%, BFR-C = 12%. The common standard deviation within group, based on the prior research was determined to be 15. Thus, to achieve a power of 80% at an α level of 0.05, 20 participants per group will be required to detect a difference between the expected means for percentage strength improvement. However, based on previous work conducted by this research group a conservative attrition rate of 20% is expected over 3 months due to voluntary patient withdrawal, death, additional hospitalisation, transfer to another facility, or patients receiving transplants [23]. Thus, a total of 75 participants will be recruited and randomly allocated to one of the three groups.

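### A block size of 4 is inconsistent with three equal arms, so the randomisation as described does not secure the group sizes the sample size assumes

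*Protocol article*

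**What the plan says.** Three statements in the protocol article bear on this.

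- **Design:** "Participants will be randomised to one of three groups", namely BFR-C, CYC and CON.
- **Sample size calculation:** one per-group figure serves all three arms: "20 participants per group will be required to detect a difference between the expected means for percentage strength improvement". After a 20% allowance for attrition, "a total of 75 participants will be recruited and randomly allocated to one of the three groups". The ratio is not written out, but 75 is 3 × 25 and 25 × 0.8 = 20, so 1:1:1 is clearly intended.
- **Randomisation:** "Randomisation will be conducted at a participant level prior to familiarisation and baseline testing", and the method "will randomise participants by blocks of 4 via a computer-generated random number sequence by an independent researcher".

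The article describes no unequal ratio, fourth arm, stratification or varying block size, and no rule for filling the fourth place in a block. Because allocation is by participant, the 4 cannot be read as a cluster of some kind.

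**The concern.** A permuted block keeps arms balanced only if its size is a multiple of the number of places in the allocation ratio. For three arms at 1:1:1 that means 3, 6, 9 and so on. A block of 4 holds each arm once and leaves one place over, so every complete block is unequal.

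This is not a detail that a condensed article may leave to the full protocol. A block size is stated, and it does not fit the group sizes stated elsewhere in the same article. A reader cannot tell what ratio the list was built to. At stake are the group sizes behind the power calculation and, depending on how the fourth place is filled, the power itself. Analysis cannot repair the list once participants have been allocated from it.

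**Working it through.** **Inputs (Sample size calculation, protocol article).** Projected changes in strength: "CON = −3%, CYC = 2%, BFR-C = 12" (per cent). Spread: "The common standard deviation within group, based on the prior research was determined to be 15". Target: "to achieve a power of 80% at an α level of 0.05". Attrition: 20%. The test is taken to be the overall F test of the one-way ANOVA named under Statistical analysis. The article does not say which test the calculation used, so this is an assumption, checked in step 1. Attrition is assumed equal across arms.

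**Formula.** With arm sizes nᵢ, means μᵢ, weighted grand mean m = Σnᵢμᵢ/N and SD σ, the noncentrality is λ = Σnᵢ(μᵢ − m)²/σ². Power is the probability that a noncentral F with 2 and N − 3 degrees of freedom exceeds the 5% critical value.

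**Step 1: reproduce the planned figure.** With 20/20/20, m = (−3 + 2 + 12)/3 = 3.667. The squared deviations are 44.44, 2.78 and 69.44, summing to 116.67. So λ = 20 × 116.67/225 = 10.37, and power is 0.809. At 19 per group it is 0.786. Hence 20 per group is the smallest size that reaches 80%. Then 20/0.8 = 25 per arm and 3 × 25 = 75. The sample size reproduces under 1:1:1.

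**Step 2: check the block size.** 4 = 3 + 1, so one place is left over in every block. By contrast 75/3 = 25 exactly.

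**Step 3: consequences under three possible rules.** None of these rules is in the article.

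*(a) Fourth place drawn at random.* In 20,000 simulated lists of 75:
- exactly 25/25/25 occurs in about 4%;
- the smallest arm has 22 or fewer in about 33%;
- the gap between largest and smallest arm has median 4 and 95th percentile 8.

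With 80% of each arm evaluable, mean power is about 0.81 and the 5th percentile is 0.78.

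*(b) Fourth place rotated.* Three blocks give 4/4/4. Eighteen blocks (72 participants) give 24/24/24. The last three participants bring this to 25/25/25 or, at worst, 26/25/24.

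*(c) One arm always doubled (2:1:1).* 75 splits as about 37.5/18.75/18.75, which at 80% is 30/15/15 evaluable.

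| Doubled arm | CON/CYC/BFR-C | m | λ | Power |
|---|---|---|---|---|
| none (plan) | 20/20/20 | 3.67 | 10.37 | 0.81 |
| CYC | 15/30/15 | 3.25 | 7.92 | 0.69 |
| CON | 30/15/15 | 2.00 | 10.00 | 0.79 |
| BFR-C | 15/15/30 | 5.75 | 11.25 | 0.84 |

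For example, with CYC doubled, λ = (15 × 6.25² + 30 × 1.25² + 15 × 8.75²)/225 = 1781.25/225 = 7.92. Doubling CYC costs most because its projected mean lies between the other two; doubling an extreme arm costs little or even helps.

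**The case against.** The best defence is that unequal blocks do not imply unequal arms. A rotated extra place ends within one participant of 25 in every arm. A random extra place costs almost no power on average. Even then blocking still does some work: simple randomisation would leave a smallest arm of 22 or fewer in about 74% of lists, against about 33% here. ANOVA is valid with unequal groups, and the sample size itself reproduces. All of this stands, and it limits how serious the point is.

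Three stronger readings are tempting and are not supported:

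- **That the scheme cannot produce equal groups.** It does not guarantee them. Rule (b) shows that near-equality or exact equality is attainable.
- **That power falls to 69%.** This needs two things the article does not say: a fixed 2:1:1 ratio, and CYC as the doubled arm. The single per-group number in the sample size argues against any 2:1:1 plan, and doubling BFR-C would raise power.
- **That 75 not being divisible by 4 is a fault in itself.** A list may run past the recruitment target, and balanced blocks of 6, 9 or 12 also leave three places over at 75.

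What the defence does not remove is the contradiction. The stated block size does not fit three equal arms, and the rule that would make it harmless is not given.

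**Conclusion.** The point holds as an inconsistency between the Randomisation section and the Design and Sample size sections. That 4 cannot be shared equally among three arms is certain. That 1:1:1 is intended is an inference, but a firm one, since both 20 per group and 75 in total follow from it.

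The effect on power runs from negligible (random or rotated fourth place) to moderate (0.69 against 0.81, in the worst of three assumed 2:1:1 schemes). These powers rest on the article's own means and SD, the overall F test, and equal 20% attrition in each arm. Nothing here biases the comparison or invalidates the analysis. It should be fixed, because the mechanism as stated does not secure the planned groups and the correction is cheap; it is not grounds for doubting the trial as a whole.

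**What to change.** In the Randomisation section, state 1:1:1 allocation and replace the block size with permuted blocks whose size is a multiple of 3, for example a mix of 3 and 6. Blocks of 3 fill 75 exactly, and so can a mix (five blocks of 3 and ten of 6: 15 + 60 = 75), giving 25 per arm. The total stays at 75 and power at 0.81 with 20 evaluable per arm.

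Before enrolment the cost is one changed sentence and a regenerated list. If enrolment has begun, report the block scheme and allocation ratio actually used, including how the fourth place in each block was assigned. If the 4 is only a reporting slip, correcting the sentence is enough.

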### Exercise intervention

Exercise training sessions will occur intradialytically for all exercising participants and will be completed within the first 2 h of the session to avoid loss of exercise training quality [24, 48]. All sessions will be supervised by a member of the research team. Exercise training sessions will consist of cycle exercise for both BFR-C and CYC groups. Both BFR-C and CYC groups will complete a total volume of 20 min cycling at a relative intensity for each participant to be dictated by rating of perceived exertion (RPE), similar to previous exercise and ESKD studies [17, 49, 50]. This will also be compared to measurements of percentage age-predicted maximum heart rate (APHR_max_) in order to determine if targeted RPE needs to be adjusted to account for potential discrepancies between patient subjective intensity and objectively observed intensity. If participants are unable to maintain the prescribed cadence at this workload for the full duration, they will be instructed to complete as much of each cycling bout as possible.

#### Age-predicted maximum heart rate

APHR_max_ will be used as a relative indicator of intensity during exercise training sessions. Approximately 50–70% of participant’s age-predicted APHR_max_ will be used as an objective target to indicate whether participants in BFR-C or CYC are exercising at the prescribed intensity for this study. This will be achieved using a fingertip heart rate monitor and pulse oximeter (CMS50, Contec Medical Systems Co., Ltd., Qinhuangdao, Hebei Province, China) placed on the second or third finger of the participant’s hand on the contralateral limb to their arteriovenous fistula. This will be measured and recorded during the final minute of each period of active cycling within a session to correspond with measures of RPE.

